#### Delivery of the intervention

i.Intervention design

The study will be implemented through a CRT targeting HCWs working in maternity and children’s wards. The intervention will be implemented over a period of 4 months, through a partnership with WaterAid Uganda, MOH, KCCA, MWE as well as selected HCFs. The design of the study was guided by the checklist for standard protocol items recommended for international trials (SPIRIT), which is provided in Additional file 1.
ii.Trial interventions

In both the intervention and control HCFs, simple innovatively designed hand hygiene facilities (tapped plastic jerricans with a stand and basin) will be provided (where needed) in delivery rooms, post-natal wards, and children’s wards. Soap and ABHR will be provided at all hand hygiene stations. Additionally, ABHR will be provided at points of patient care and on medication trolleys. Hand hygiene demonstrations using the “glo germ” gel will be done in both study arms at the beginning of the study. The choice of the departments/wards for the interventions is based on the understanding that mothers and neonates face the greatest risk of infections related to poor WASH and IPC measures in HCFs [35], but these wards will also allow the research team to maximize the observations of hand hygiene opportunities while standing within a radius of about 5–10 m [36].

In the intervention HCFs, besides the provisions in the control group, two interventions, mhealth and environmental cues (nudges) that have been successful in enhancing adherence to treatment guidelines and enhancing hand-hygiene in school going children [19, 22] respectively will be used. The choice of the specific mhealth and nudges intervention, and the frequency of exposure to mhealth messages among the study participants will be determined in the insight workshop. The mhealth intervention messages will be designed with a focus on: benefits of hand hygiene; when to do hand hygiene; how to do hand hygiene and how to protect others. However, the messages will also have educational jokes and response prompts where HCWs with the highest number of responses will win hand hygiene supplies. This will be critical in enhancing participant retention and complete follow-up. The educational messages and jokes in the mhealth intervention will be guided by the results from the formative study.

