Secondly, hand rinsates from HCWs participating in the CRT will be collected immediately after the hand hygiene observations during baseline and end-line. The samples (hand rinsates) will be collected by a team of trained environmental health officers. During sampling of hand rinsates, HCWs will put their hands, one at a time in Whirl-Pak bags containing distilled water. The HCWs will wash their hands by rubbing the inner hands for about 2 min and the enumerator massaging their hands from outside the whirl pak bag to remove any potential pathogens. Aseptic techniques will be used to collect duplicate samples from each of the study participants (HCWs) during baseline, midline and end-line. The samples will be stored in sterile plastic bottles and transported on ice to the laboratory for further analysis within 4 h. The hand rinsates will be analysed for *Escherichia coli (E.coli)*, to establish if there are differences in the levels of contamination on the hands of the HCWs before and after the intervention. During analysis, hand rinsates will be diluted using the ratios of 1:1, 1:10 and 1:100. The membrane filtration method (with Chromocult agar) will be used to concentrate samples, and incubation will be done at 37 °C for 24 h. Colonies of *E.coli* will be identified by their dark blue to violet colour, and they will be counted and recorded per 100 ml of sample.

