#### Data analysis

i.Qualitative analysis (formative stage)

The KIIs will be transcribed verbatim by two experienced transcribers. The typed transcripts will then be read several times by all members of the study team who will then develop codes. Code book definitions will be based on the objectives of the study while integrating in emerging themes from the data. The code book will be discussed and agreed upon by the study team. Then two experienced research assistants (RAs) will code the articles using ALTAS-ti software to ease further analysis. The code reports will then be read and discussed by all the investigators who will agree on both codes and categories. Then, codes will be grouped into categories, themes and subthemes [40].
ii.Quantitative analysis (effect of intervention)

The effect of the intervention will be evaluated at two time-points: midway the intervention, and immediately after the completion of the intervention period to assess the short-term effects on hand hygiene. Data from all surveys will be double entered into Open Data Kit (ODK) collect, and statistical analysis will be carried out using Stata version 14. We will calculate the prevalence of cluster level hand hygiene at baseline and follow-up for each HCF. Mixed sub-group analysis will be stratified by sex, cadre, experience, and level of training. We shall run multivariable logistic regression under the generalised estimating equations (GEE) framework to account for the dependence of hand hygiene on the intervention in a marginal way. This approach will give population average estimates for effect of intervention while accounting for other covariates in the model. An exchangeable correlation structure will be considered. Table 3 provides a summary of the study objectives, methods and data analysis procedures.

**Table 3 Tab3:** Summary of study objectives, methods and data analysis procedures

Objectives	Study population	Data collection methods	Indicators	Data analysis
Explore the facilitators for enhancing healthcare workers’ hand hygiene practices in HCFs in the GKMA.	Healthcare workers in selected HCFs and district leaders.	Key informant interviews	Facilitators of Hand hygiene among HCWs	i. Thematic content analysis
		Semi-structured interviews	Facilitators of Hand hygiene among HCWs	i. Thematic content analysis ii. Descriptive statistics
	Healthcare facilities	Observations	Facilitators of Hand hygiene among HCWs	i. Descriptive statistics

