Explore the barriers for enhancing healthcare workers’ hand hygiene practices in HCFs in the GKMA.	Healthcare workers in selected HCFs.	Key informant interviews	Barriers of Hand hygiene among HCWs	i. Thematic content analysis
		Semi-structured interviews	Barriers of Hand hygiene among HCWs	i. Thematic content analysis ii. Descriptive statistics
	Healthcare facilities	Observations	Barriers of Hand hygiene among HCWs	i. Descriptive statistics
Determine the impact of mobile phone WASH messages and environmental cues on hand hygiene practice among health workers in HCFs in the GKMA.	Healthcare workers in selected HCFs.	i. Observations of healthcare workers ii. Laboratory analysis of hand rinsates for *E.coli*	i. Percentage change (increase or decrease) in the used hand hygiene opportunities ii. Percentage change (increase or decrease) in the number of E.coli colonies/100 ml of samples of hand rinsates	i. Use of statistical tests - McNemar test - Paired t-test - GEE Logistic regression

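### Table 3 lists before-after paired tests with no stated role for the impact objective, and no listed method suits a between-arm comparison of E. coli concentration

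*Protocol article*

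**What the plan says.** In the Data analysis section of the protocol article, Table 3 summarises the methods for each objective. For the third objective, the impact of messages and cues, the analysis cell reads "Use of statistical tests - McNemar test - Paired t-test - GEE Logistic regression". It does not say which test applies to which outcome or which one carries the conclusion. The two indicators in that row are "Percentage change (increase or decrease) in the used hand hygiene opportunities" and "Percentage change (increase or decrease) in the number of E.coli colonies/100 ml of samples of hand rinsates"; neither names a comparison between arms.

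The text of the same section, under the quantitative analysis of the intervention effect, names only multivariable logistic regression under GEE. It says of it: "This approach will give population average estimates for effect of intervention while accounting for other covariates in the model", and adds "An exchangeable correlation structure will be considered". The Abstract also names only GEE. Neither place mentions McNemar or the paired t-test.

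The Outcome measurement section gives the purpose of the rinsate analysis as "to establish if there are differences in the levels of contamination on the hands of the HCWs before and after the intervention". The measurement is an E. coli colony count per 100 ml.

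Under Delivery of the intervention, both arms receive hand hygiene stations where needed, soap and hand rub. In addition, "Hand hygiene demonstrations using the “glo germ” gel will be done in both study arms at the beginning of the study". The sample size paragraph assumes a 5% rise in the control arm, and the limitations paragraph expects COVID-19 to influence hand washing behaviour.

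**The concern.** The trial asks what messages and cues add to supplies that both arms receive, and only a contrast between randomised arms answers that. A paired test compares a healthcare worker with himself or herself at baseline. The change it measures contains everything that happened between the two rounds, including components given to both arms and a secular change that the protocol itself expects. It also treats workers as independent, so any facility-specific shift between rounds is ignored.

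Because Table 3 assigns no roles, a significant before-after change in the intervention arm (or in that arm and not in the other) could be reported as impact while following the protocol. The exposure is greatest for E. coli. The stated purpose is itself before versus after, logistic regression does not model a concentration, and the paired t-test is the only listed test that takes a quantitative outcome.

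**Working it through.** The plan gives no figure for how these tests behave, so there is none to reproduce. The check asks how often each test is significant when messages and cues do nothing and both arms rise equally.

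**Inputs from the protocol article.** 15 facilities and 225 workers per arm; control proportion 0.747; 5% rise in the control arm; two-sided 5% level (1.96); design effect 2.0; 20 opportunities per worker.

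**Assumptions not in the documents.** SD of a worker's change in proportion, 0.20 to 0.30. For McNemar, a yes/no status per worker from a latent normal model with facility variance 0.07-0.10, individual variance 0.2-0.5 and facility-by-period variance 0-0.07.

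**Size of the shared rise.** The 5% can be read in two ways:
- 5 points: 0.747 to 0.797, a change of 0.05.
- Relative: 0.747 × 1.05 = 0.784, a change of 0.747 × 0.05 = 0.03735.

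**Paired t-test in the intervention arm, true effect zero.** z = change / (SD/√225) = 15 × change / SD, and the rejection rate is approximately Φ(z − 1.96).

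| SD of change | z, 5 points | rejects | z, relative 5% | rejects |
|---|---|---|---|---|
| 0.20 | 3.75 | 96% | 2.80 | 80% |
| 0.25 | 3.00 | 85% | 2.24 | 61% |
| 0.30 | 2.50 | 71% | 1.87 | 46% |

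**McNemar in the intervention arm, true effect zero** (simulation, 15 facilities of 15 workers per arm):
- Relative 5% rise: about 19-23%.
- 5-point rise: about 29-33%.
- Shared 10-point rise: about 75-91%.

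**Between-arm t-test on facility-level change, same simulated data:** 4-6% throughout, as it should be.

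**Clustering alone, with no shared rise.** Pairing removes a facility effect that is constant over time. McNemar then rejects at about 5%, and at about 12-13% with an assumed facility-by-period variance of 0.07. If the full design effect of 2.0 applied to the change scores, the rate would be 2 × P(Z > 1.96/√2) = 16.6%. The protocol gives that design effect for clustering of workers within facilities, not for change scores, so 16.6% is conditional.

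**E. coli, method by method.**
- McNemar needs a paired yes/no, and the outcome is a concentration.
- The paired t-test takes a quantitative value but compares rounds, not arms.
- Logistic GEE can contrast arms, but for a binary outcome; the text on GEE speaks only of hand hygiene.

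None of the three gives a between-arm comparison of a concentration.

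**The case against.** The strongest reply is that the between-arm analysis is already planned. The text and the Abstract name one inferential method, logistic GEE, and the paired tests appear only in a summary table whose same cell lists GEE. That stands for hand hygiene. A reader might infer from Table 3 that the trial has no valid between-arm analysis of its primary outcome; the documents do not support this.

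A reader might also infer that the paired tests will show impact whatever happens. That is conditional on a change over time shared by both arms, and on someone treating a before-after p-value as the result. With no shared change and stable facility effects, McNemar keeps its 5% level. Nor does the article say outright that the paired tests run within one arm, although the paired form and the change indicators make before-after the natural reading. Pooling both arms would still ignore allocation.

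Three further criticisms rest on details the article leaves open:
- That McNemar has no usable input. The sample size paragraph speaks of the proportion of workers who practise hand hygiene, which implies a yes/no per worker.
- That percentage change fails at a zero baseline. This holds only if change is computed per worker.
- That the t-test would use raw counts. A transformation may be specified elsewhere.

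What the reply does not reach is the lack of any assigned role for the paired tests and the absence of a suitable listed method for E. coli.

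**Conclusion.** The point holds in this form. Table 3 places before-after tests beside GEE for the impact objective with no hierarchy, and such tests cannot separate messages and cues from what both arms receive. For hand hygiene the damage is limited to ambiguity, because GEE is named as the effect analysis. For E. coli the method as stated is wrong for the question.

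The size depends on three things: a shared rise equal to the protocol's own control-arm figure, the reading of that 5%, and the assumed variances set out above. Across those assumptions, one-arm before-after tests would be significant far more often than 5% without any true effect, while the between-arm comparison stays near its nominal level.

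**What to change.** 1. State that impact on both outcomes is judged only by the contrast between arms: the arm effect adjusted for the baseline value, or the arm-by-time interaction, with the facility as the cluster. For hand hygiene, apply it at the planned midline and end-line rounds.
2. For E. coli, name a model suited to counts or to a log-transformed concentration, for example negative binomial GEE or log10(count + 1), adjusted for baseline and clustered on facility. End-line is the natural round, since both descriptions of rinsate sampling in the Outcome measurement section include it.
3. Delete McNemar and the paired t-test from Table 3, or label within-arm change as descriptive and report it without p-values.
4. Reword the rinsate purpose (now "differences in the levels of contamination on the hands of the HCWs before and after the intervention") and both percentage-change indicators in Table 3 as comparisons between arms.

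The cost is analysis wording only. Baseline and follow-up measurements of both outcomes are already planned, so no visit, sample or participant is added.

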### Quality assurance/ quality control of data and collection

Experienced RAs including observers will be recruited from a well-established network of RAs that have participated in successful research projects. These will be trained on research ethics, research design and how to minimize bias. Prior to data collection, there will be a pre-test of the data collection tools to ensure they are valid and reliable. This will also enable RAs to familiarise with the data collection tools and also correct any errors if discovered. Pretesting will be in Nyimbwa health centre IV, Luweero district. This HCF has been purposively selected because it shares similar characteristics with some of the HCFs in the GKMA. A quality control team will be instituted whose role will be to ensure that RAs adhere to the approved study procedures. To ensure quality in quantitative data entry, the data entry screen will be designed with skips and restrictions. In case of samples for hand rinsates, a duplicate sample of the hand rinsates will be obtained for validation of results.

### Dissemination plan

Study findings will be presented at appropriate international conferences and submitted for peer-reviewed publication. Besides, study findings will be disseminated in stakeholders’ meetings and to the HCWs and managers in study HCFs.

## Discussion

Hand hygiene is a paramount intervention in the prevention of healthcare acquired infections. However, the rate of adherence to hand hygiene during patient care remains as low as 15% among HCWs [41]. Besides, only a few studies have attempted to holistically understand the facilitators and barriers to hand hygiene among HCWs, and the impact of use of mobile phone text messages and environmental cues [21]. Therefore, our study will explore the facilitators and barriers to adherence to hand hygiene, and the impact of mhealth and environmental cues on hand hygiene practices among HCWs working in maternal and children’s wards.

Our study will be a cluster randomized trial in which HCWs in public HCFs in the GKMA will be assigned to the intervention and control arms. Cluster randomized trials have the potential to minimise potential biases such as confounding, and are therefore considered as the gold standard for generating the highest level of evidence [42]. HCWs in both the intervention and control arms will be exposed to simple innovatively designed hand washing facilities (tapped plastic jerricans with a stand and basin) which will be placed in delivery rooms, post-natal and children’s wards. Delivery rooms, post-natal and children’s will be considered since they present mothers, children and HCWs with an elevated risk to healthcare acquired infections, especially blood borne pathogens such as HIV, hepatitis B virus, *Staphylococcus aureus* and *Streptococcus pneumonia* [43, 44].

Though not widely studied, having simple hand washing facilities such as plastic jerrycans and tippy taps have been shown to increase adherence to hand hygiene at critical times at community level [45, 46]. Therefore, our study will utilise this intervention based on the notion that having simple innovatively designed hand hygiene facilities and the required supplies will increase the level of adherence. In addition to the interventions in the control arm, HCWs in the intervention arm will be exposed to environmental cues and mobile text messages on hand hygiene. Also, evidence from a simulation hospital study in a US medical centre and affiliated medical school indicated that environmental cues subconsciously influenced the hand hygiene practice [47]. Similarly, mobile text messages have also been reported to influence behaviour change in a number of healthcare interventions [48, 49]. However, their impact on promotion of hand hygiene in HCF settings is still understudied [21]. Mobile text messages are anticipated to promote adherence to hand hygiene by reminding HCWs to wash hands or use ABHR during the critical moments of patient care.

The impact of the environmental cues and mhealth intervention will be assessed based on adherence to the WHO’s 5 moments for hand hygiene [50] and *Escherichia coli* (E.coli) concentration levels in hand rinsates from HCWs. The WHO 5 moments of hand hygiene have widely been used in evaluating hand hygiene interventions in healthcare settings [50–52]. Similarly, *E. coli* has also been used as an indicator for measuring the effectiveness of hand hygiene in HCFs [53–55].

### Strengths and limitations of the study

To the best of our knowledge, this may be the first study to evaluate the impact of environmental cues and mhealth on hand hygiene practice among HCWs. However, observations of hand hygiene practice among HCWs are likely to be affected by social desirability bias. To solve this challenge, RAs that will undertake the observations will be trained, standard WHO observation tools will be used, and where possible two observers will be used to observe hand hygiene behaviour simultaneously. In addition, our findings are likely to be influenced by a change in hand washing behaviour, which could be attributed to the recent COVID-19 pandemic. The effect of COVID-19 will be factored in during data analysis through stratification of data.

### Trial status

The study has received ethical approval from the Makerere University Higher Degrees Research and Ethics, and was consequently registered by the Uganda National Council of Science and Technology. Administrative permission to conduct the study has also been obtained from the 3 study districts. Currently, we are conducting the formative study phase, which is being implemented through literature review, key informants’ interviews, semi-structured interviews and observations in HCFs. The intervention is set to begin in February 2021.

## Data Availability

This protocol doesn’t include any data yet, and readers are requested to ask the authors for data once available.

## Abbreviations

ABHR: Alcohol Based Hand Rub
BCD: Behavior Centered Design
CRT: Cluster Randomized Trial
DMC: Data monitoring committee
GEE: Generalized estimating equations
GKMA: Greater Kampala Metropolitan area
HCAIs: Healthcare acquired infections
HCFs: Healthcare facilities
HCWs: Healthcare workers
IPC: Infection Prevention and Control
JMP: Joint Monitoring Programme
KCCA: Kampala Capital City Authority
LMICs: Low and middle income countries
MOH: Ministry of Health
MWE: Ministry of Water and Environment
NAS: National Academy of Sciences
NGO: Non-Government Organization
ODK: Open Data Kit
SMS: Short message service
UNICEF: United Nations Children’s Fund
WASH: Water, sanitation and hygiene
WHO: World Health Organization
